#### The Control Group

Participants assigned to the CG received a booklet in which cognitive games were illustrated. Moreover, suggestions on how to live a healthy life with active aging were provided in the booklet. At the beginning of the trial, the participants in the CG were invited to follow the booklet, play the cognitive games, and follow the suggestions, but they were neither motivated nor contacted during the experiment, unless they wished otherwise.

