### Data Analysis

This subsection describes the measurements, statistical tests, and tools with which the data collected in the engAGE PoC were, and are still being, analyzed. The different types of data that were collected in the engAGE project are as follows:

Credentials: username, password, email address, and similar security information used for authentication and account access in different services of the platformPersonal data: first name, last name, gender, age, weight, height, email address, contact address, and phone number of older adults in different services of the platformAnswers to specific questions in self-assessment questionnaires on MEMASGames score from Pepper appsMeasurements and monitored parameters: weight, heart rate, blood pressure, and physical activities gathered through the monitoring infrastructureHistorical data of the measurements and monitored parameters for training and using ML algorithms for each older adult in the ML service

In the engAGE testing and evaluation phase, the following data were, and are being, processed:

Information and results from questionnairesCognitive game scoresHistorical data of measurements collected for each end userAny information the end users decided to share through discussions/interviews, as well as data providing feedback from trialsOutcomes that concern feasibility (ie, the primary interest of the engAGE PoC): recruitment rate (proportion of eligible individuals who consent to participate in the study, ie, those who attended more than 80% of weekly sessions), retention rate (proportion of participants who completed the 6-month intervention period), and adherence to the intervention (average number of interactions with the Pepper robot during weekly sessions, the frequency of use of the MEMAS app, and the activity tracker recording time)

Descriptive statistics (means, SDs, medians, IQRs) will be used to summarize adherence metrics.

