Outcomes that concern efficacy of the engAGE intervention were considered exploratory and dealt with the metrics about cognitive capacity, quality of life, social dimension, and stress and care load relief (for caregivers). In particular, to explore the potential efficacy, changes in these domains before and after the intervention were analyzed. Paired *t* tests (for normally distributed data) or Wilcoxon signed-rank tests (for nonnormally distributed data) were used to compare pre- and postintervention scores within each group, while independent samples *t* tests or Mann-Whitney U tests were performed to assess between-group differences in change scores. Moreover, effect sizes (Cohen d or Cliff δ) were calculated to quantify the magnitude of any observed differences. Due to the nature of the PoC, this study was not powered to detect statistical significance. *P* values will be reported without adjustments for multiple comparisons and interpreted with caution. All analyses were planned for descriptive purposes, and only participants with at least 80% of adherence to the intervention were considered for analysis.

The aforementioned analyses were also applied to acceptance and usability measurements (ie, UTAUT and SUS scores) that provided insights into the primary goal of the study: the feasibility of the intervention. Data from the ML service were analyzed to correlate physical activity, sleep parameters, game scores, and self-assessment data. Longitudinal data analysis techniques (eg, mixed effects models) were used to analyze changes in these parameters over time and assess potential correlations with cognitive and quality-of-life outcomes.

The first step in the data analysis dealt with the description of the sample. Continuous variables will be reported as either the mean (SD) or the median (IQR) on the basis of their distribution (assessed using the Kolmogorov-Smirnov test). Categorical variables will be expressed as an absolute number and percentage. Mann-Whitney U tests (for nonnormal distribution) or chi-square tests (for normal or nonnormal distribution) were used to compare independent and dependent variables between the pre- and postintervention conditions, in addition to simple descriptive statistics (means, medians, and SDs, as appropriate).

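### Restricting analysis to participants with at least 80% adherence means the between-group comparison is no longer between the groups as randomised, and the rule is undefined for the control group

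*Protocol article*

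**What the plan says.** All references are to the protocol article.

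- **Analysis set (Data Analysis).** The sentence that fixes the set opens with "All analyses were planned for descriptive purposes" and ends with "only participants with at least 80% of adherence to the intervention were considered for analysis". No other set is named.
- **Comparison affected (Data Analysis).** For the change scores, "independent samples *t* tests or Mann-Whitney U tests were performed to assess between-group differences in change scores", with Cohen d or Cliff δ as effect size. Under Recruitment, participants are randomly assigned to EG or CG.
- **What adherence means (Data Analysis).** Among the feasibility outcomes it lists "adherence to the intervention (average number of interactions with the Pepper robot during weekly sessions, the frequency of use of the MEMAS app", together with tracker recording time.
- **Other feasibility rates (Data Analysis).** The recruitment rate is explained as "proportion of eligible individuals who consent to participate in the study, ie, those who attended more than 80% of weekly sessions". Next to it stands the "retention rate (proportion of participants who completed the 6-month intervention period".
- **Acceptance and usability (Data Analysis).** After the sentence with the 80% rule, the text continues: "The aforementioned analyses were also applied to acceptance and usability measurements (ie, UTAUT and SUS scores".
- **Control condition (The Control Group).** CG participants receive a booklet at the start, and "they were neither motivated nor contacted during the experiment, unless they wished otherwise".

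**The concern.** Randomisation makes the two arms comparable at the start. Selecting within an arm on behaviour observed later gives up that comparability, because people who keep attending may differ in prognosis from those who stop. Every adherence component the article names belongs to the EG intervention, so the rule cannot work alike in both arms as written. A difference in change scores could then reflect who stayed with the programme and not what the programme did.

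Two things are at stake. The Limitations section wants the findings to inform future sample size calculations, so a distorted effect size would be passed on to the next trial. The article also calls feasibility its primary interest and ties UTAUT and SUS to it. If those scores come only from people who used the platform enough, the people with most to say about its problems are under-represented.

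**Working it through.** **Is there a figure to reproduce?** No. The article gives no expected adherence, no retained share and no sample size calculation. The enrolment figures agree with each other: 40 + 9 = 49, 40/49 = 81.6%, 9/49 = 18.4%.

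**Is the rule workable as written?** Three gaps appear when the passages are set side by side.

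1. Adherence has three components, and the text does not say which one the 80% refers to or how they combine.
2. The analysis rule says at least 80%, while the gloss on the recruitment rate says more than 80% of weekly sessions.
3. None of the three components exists for the CG, and no CG threshold is given.

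**How large could the selection effect be?** Assumptions, none of them from the article: adherence propensity and cognitive change are jointly normal with correlation r; the true effect is zero; a fraction f of the EG with the highest adherence is kept; the CG is not filtered.

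Shift of the EG mean in SD units = r × φ(z)/f, with z = Φ⁻¹(1 − f).

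- f = 0.9: φ(z)/f = 0.1755/0.9 = 0.195. Shift 0.04 at r = 0.2 and 0.08 at r = 0.4.
- f = 0.7: φ(z)/f = 0.3477/0.7 = 0.497. Shift 0.10 at r = 0.2 and 0.20 at r = 0.4.
- f = 0.5: φ(z)/f = 0.3989/0.5 = 0.798. Shift 0.16 at r = 0.2 and 0.32 at r = 0.4.
- r = 0: the shift is 0 whatever f is.

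**Effect on the test.** Two-sample t tests were simulated under no true effect (20,000 runs, 40 EG enrolled against 9 CG, two-sided 5% level assumed because the article states none). For r from 0.3 to 0.5, the rejection rate was 7.1% to 11.3% with 70% of the EG kept and 9.2% to 18.1% with 50% kept. At r = 0 it stayed at about 5%.

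**Precision.** The standard error of the standardised difference is √(1/40 + 1/9) = 0.37 with everyone included. With 20 EG participants left it is √(1/20 + 1/9) = 0.40. Analysing everyone does not worsen precision.

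**Session attendance, if the rule also covers the adherence summaries.** One session a week for 6 months is about 26, and 0.8 × 26 = 20.8, so at least 21 sessions. Three attendance distributions were assumed (beta-binomial), with true means of 75%, 67% and 50%. Among those reaching 21 sessions, the mean would appear as 89%, 88% and 86%, while only 47%, 31% and 9% of participants reach it.

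**The case against.** The strongest defence is that the article calls efficacy exploratory and the analyses descriptive, says the study was not powered, promises cautious reading of P values, and defers proof of efficacy to a larger trial. It also records losses, discontinuations and exclusions in both groups. This limits what may be concluded, and no confirmatory claim rests on the set. It does not remove bias from an effect size, and disclosing exclusions does not correct for them. A separate analysis plan may exist, but the article does not leave the set open: it states which participants were analysed.

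Several stronger readings are tempting, and on these the defence is right.

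- **That all CG participants enter the comparison unfiltered.** The article does not say so. Table 1 lists an ad hoc questionnaire for adherence, and the CG is exempt only from the midterm evaluation, so a final question on booklet use is conceivable. What stands is that the rule is undefined for the CG. Even if it were defined, following a booklet and attending robot sessions are different behaviours, so the two retained subsets need not be comparable.
- **That reported adherence is at least 80% by construction.** The adherence metrics stand in a separate feasibility list, and a retention rate needs non-completers in its denominator. Truncation follows only if the opening words of the rule are meant to cover that list, and then surely only for the component to which the 80% refers.
- **That the UTAUT and SUS results are circular.** Carrying over the analyses may mean the tests and not the set. Carry-over of the set is the natural reading but not the only one. It would be selection on a likely consequence of acceptance, not circularity. The midterm evaluation may also have captured people who stopped later.
- **That the bias must favour engAGE.** Direction and size depend on a correlation the article does not give. The illustrated shifts of 0.10 to 0.32 SD are smaller than one standard error (0.37 SD) of the enrolled comparison.

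**Conclusion.** The concern holds for the randomised comparison. The only stated analysis set is chosen on a post-randomisation variable that is measured through EG components and has no definition for the CG, so the tests and effect sizes for change scores do not compare the groups as randomised. The possible distortion is about 0.10 to 0.20 SD with 70% of the EG kept and 0.16 to 0.32 SD with 50% kept. This assumes a correlation of 0.2 to 0.4, filtering of the EG only and no true effect; at zero correlation it vanishes.

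The feasibility part holds conditionally. If the set carries over to UTAUT and SUS, those who stopped using the platform are under-represented; if it covers the adherence summaries as well, session attendance is truncated at 80%. A reader might infer that all feasibility results were drawn from a set without the failures. The article does not establish that.

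**What to change.** - Make the main between-group analysis all randomised participants in the arm assigned, using every available final (6-month) assessment regardless of adherence.
- Report retention and adherence on all enrolled EG participants (40).
- Report UTAUT and SUS on all EG participants with an available assessment, showing the denominator and what is missing at each time point.
- Keep the 80% set only as a labelled supplementary description of the EG, not as the basis of a between-group test. State which adherence component the 80% refers to, and use one form of the threshold throughout.

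The cost is a change of wording and a re-run on the data available. The estimates may be less favourable. Complete data on all 40 EG participants should not be promised: the consent section treats signs of dissent as automatic withdrawal, and the security section grants a right to erasure, so some assessments may not exist or may no longer be usable.

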**Second evaluation (after 3 months of use):**
The aim of the midterm evaluation was to collect useful information about the use of the engAGE (Managing Cognitive Decline Through Theatre Therapy, Artificial Intelligence, and Social Robot–Driven) platform after a short period of use for detecting and analyzing technology acceptance and usability issues. Obviously, the control group (CG) was not evaluated at this stage.

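### Data Analysis gives two incompatible tests for the same pre-post contrast, one of them for independent samples, and carries a between-arm comparison over to UTAUT and SUS that has no meaningful control

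*Protocol article*

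**What the plan says.** All of this is in the protocol article.

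- **Data Analysis, paragraph on exploratory efficacy.** For change over time, paired t tests or "Wilcoxon signed-rank tests (for nonnormally distributed data) were used to compare pre- and postintervention scores within each group". For the arms, "independent samples *t* tests or Mann-Whitney U tests were performed to assess between-group differences in change scores".
- **Data Analysis, next paragraph.** "The aforementioned analyses were also applied to acceptance and usability measurements (ie, UTAUT and SUS scores"). It ties these measures to feasibility, which it calls the primary goal of the study.
- **Data Analysis, paragraph that opens with the description of the sample.** Mann-Whitney tests, for nonnormal data, or "chi-square tests (for normal or nonnormal distribution) were used to compare independent and dependent variables between the pre- and postintervention conditions".
- **Study Design.** A before-and-after design, with data collected on the enrolled individuals before and after the technology was installed and used.
- **The Control Group.** Control participants received a booklet of cognitive games and healthy-living suggestions.
- **Textbox 1.** Baseline comes before the start of the PoC. The 3-month evaluation looks at acceptance and usability, and of it the article says "Obviously, the control group (CG) was not evaluated at this stage". A final evaluation follows at 6 months.

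**The concern.** Pre and post scores come from the same participants, so they are paired. The Mann-Whitney test and the ordinary chi-square test treat the two sets of scores as if they came from different people, and so ignore the pairing. Describing chi-square as suitable for normal or nonnormal distributions is a second error: it is a test on categorical counts, to which normality does not apply.

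The paired tests are named two paragraphs earlier for the same contrast, so a reader cannot tell which test lies behind a reported pre-post P value. P values will be reported, and under Limitations the findings are meant to inform later sample size calculations.

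The UTAUT and SUS sentence raises a separate problem. It brings in a between-arm comparison of change in the acceptance and usability of a platform that one arm was not given, and a before-use comparison on a scale that presupposes use.

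**Working it through.** **1. Two rules for one contrast.** The article states no power or alpha to reproduce, so the first check sets the sentences side by side.

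| Place in Data Analysis | Contrast | Test | Suitable? |
|---|---|---|---|
| Efficacy paragraph | Pre vs post, within group | Paired t / Wilcoxon signed-rank | Yes |
| Efficacy paragraph | Change scores, experimental vs control | Independent t / Mann-Whitney | Yes |
| Sample-description paragraph | Pre vs post conditions | Mann-Whitney / chi-square | No, data are paired |

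The third row cannot easily be read as a baseline comparison of arms, because the sentence says the tests "were used to compare independent and dependent variables between the pre- and postintervention conditions".

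**2. Direction of the error.** For n pairs with common SD and pre-post correlation r, the standard error of the mean change is SD × √(2(1−r)/n). An unpaired test uses SD × √(2/n). The ratio is 1/√(1−r), which is 1.2, 1.4, 1.8 and 2.2 at r = 0.3, 0.5, 0.7 and 0.8. The unpaired standard error is too large, so the test rejects too seldom.

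**3. Size of the error.** Inputs:

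- n = 40, the experimental-group enrolment given in Results. The analysed number may be smaller, because Data Analysis keeps only participants with at least 80% adherence.
- Two-sided 0.05, r from 0.3 to 0.8, and shifts of 0.3 and 0.5 SD. These are assumptions; the article gives none of them.
- Simulated bivariate normal scores.

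| r | Mann-Whitney type I error | Power at 0.3 SD: Mann-Whitney / Wilcoxon signed-rank | Power at 0.5 SD: Mann-Whitney / Wilcoxon signed-rank |
|---|---|---|---|
| 0.3 | about 2% | 21% / 33% | 59% / 72% |
| 0.5 | about 0.7% | 18% / 44% | 60% / 85% |
| 0.7 | about 0.1% | 13% / 65% | 63% / 97% |
| 0.8 | about 0.01% | 10% / 82% | 66% / 99.8% |

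The Wilcoxon signed-rank test keeps its type I error near 5% throughout. As a share of the paired test's power, the loss runs from (72−59)/72 = 18% (r = 0.3, 0.5 SD) to (82−10)/82 = 88% (r = 0.8, 0.3 SD).

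For the 9 control participants at r = 0.5 and a 0.5 SD shift, power is about 8% against 22%. For paired binary data (n = 40, prevalence 0.5, no change), the ordinary chi-square test rejects about 2.1%, 0.7% and 0.1% of the time at phi = 0.3, 0.5 and 0.7.

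**4. UTAUT and SUS.** The sentence that extends the tests to these scales comes before the Mann-Whitney/chi-square sentence. What it carries over is therefore the pair of rules in the efficacy paragraph.

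- *Between-group change.* The control group received a booklet and not the platform, so a control change score for platform acceptance or usability has no meaning.
- *Pre-use to post-use.* A usability score taken before any use of the system is not meaningful.
- *Under use.* Experimental-group scores at 3 and 6 months are possible and would support a paired comparison.

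**The case against.** The strongest reply is that a correct plan is on the page. The efficacy paragraph names the right tests for both contrasts, and the faulty sentence sits in a paragraph that begins with describing the sample. That stands: the defect is one contradictory sentence, and a reader who inferred that the unpaired tests are the plan would go too far.

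It is also fair that the error is conservative. A reader might infer spurious positive findings from the wrong test, but with positive correlation the opposite happens. Nor can it be said that the unpaired test always loses most of the power. At a 0.3 SD shift that is true from r = 0.5 upward; at 0.5 SD the loss is about a fifth to a third. Both depend on values the article does not give.

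On UTAUT and SUS, a reader might infer that no data for these tests can exist. The article does not support that:

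- Goal of the Study says all measurements were made at the beginning and end, so a baseline UTAUT on expectations is not excluded.
- Experimental-group data at 3 and 6 months are possible.
- The statement that the control group was not evaluated concerns the 3-month visit only.
- The article does not set out visits and respondents for the two scales (Table 1 lists SUS under the informal caregiver). A condensed article may leave that schedule to the full protocol.

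The objection does not rescue the sentence itself, which is wrong as written, or the between-arm UTAUT/SUS contrast.

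**Conclusion.** The point holds as an internal contradiction, with moderate severity. Data Analysis states a correct paired rule and an incorrect unpaired rule for the same pre-post contrast, and mislabels chi-square. Any pre-post P value from the unpaired rule would be too large whenever pre and post scores correlate positively. Under the stated assumptions the nominal 5% test would run at between about 2% and 0.01%, with a power loss that ranges from modest to severe.

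The severity goes no higher because the section calls efficacy exploratory and all analyses descriptive, says the study was not powered, and asks for caution with P values; no decision rule depends on them. The contradiction leaves room to choose a test after seeing the data, but nothing in the article shows that this happened.

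For UTAUT and SUS the conclusion is limited: the between-arm change has no meaningful control, and a pre-use SUS has no meaning. Comparisons within the experimental group under use remain valid.

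**What to change.** 1. Delete or correct the Mann-Whitney/chi-square sentence in the sample-description paragraph. For pre-post data, keep paired t or Wilcoxon signed-rank tests for scores, and use McNemar (or Bowker for more than two categories) for paired categorical variables.
2. Keep Mann-Whitney and chi-square or Fisher tests for experimental versus control comparisons, and drop the reference to normality for chi-square.
3. The article reports that the analysis is complete and the results are still to be published. Before publication, confirm which test produced each pre-post P value and re-run any that were unpaired.
4. For UTAUT and SUS, report experimental-group values at the visits under use with 95% confidence intervals, and the paired 3-to-6-month change where both were collected. State respondent and visit, and make no control-group contrast. If a baseline UTAUT on expectations was taken, label it as such.

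The cost is a few lines of text and, at most, a short re-run on data already in hand.

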### Ethical Considerations

#### Ethics Approval

To guarantee the observance of ethics, the principles of the Declaration of Helsinki [36] and Good Clinical Practice guidelines were adhered to, and the study was initiated following receipt of an evaluation and approval by national independent ethics boards in two of the three countries: the Ethic Committee of the IRCCS INRCA in Italy (protocol number 6293/2023) and by the Commission cantonale d’éthique de la recherche (CCER) in Switzerland (project ID 2023-00774). Due to national laws, ethical approval was not needed in Norway, since the study fell within the technological scope. The study protocol is publicly accessible at ClinicalTrials.gov (registration number NCT06302686).

#### Ethical Issues

Technological dependence, especially on artificial intelligence (AI) technologies, represents a major ethical dilemma today for the scientific community. To limit the risk, the European Commission’s international programs have introduced guidelines for conducting studies that require the introduction of a new technology, called *responsible innovation* [37]. The core principles of responsible innovation were also applied in the engAGE project. A strategy underlying the prevention of technological dependence includes different actors around older adults in the process of acquiring skills and daily use of technology. In this way, technological solutions, such as those proposed by engAGE, respond to the definition of a sociotechnological system rather than a technological system, since they are placed in a care context that does not involve the replacement of the caregiver but stimulates the user to play a leading role in the management of their health. The services proposed are intended to support the maintenance or improvement of cognitive abilities through specific activities and do not replace (in whole or in part) the support from professional services. During the installation of the technology, moreover, information is provided to the caregiver about the limits of the technology, which can in no way replace the role of the familiar and formal assistant but only assist in some activities.

During the use of robotic platforms or, in general, technological applications, a general difficulty in distinguishing between the artificial world and reality may occur. Especially in the case of vulnerable populations, such as older adults, the interaction may generate a general feeling of attachment and dependency. To avoid this, engAGE has been designed to not look as a human but to preserve artificial aesthetics, as suggested by the guidelines [38]. In addition, during the first contact with the participants and also during the intervention, researchers are in contact with the users, continuously stimulating awareness about the technological applications, as well as monitoring the appropriateness of the use of the solution in terms of the users’ autonomy, specific needs, and personal preferences. Following the recommendations provided by the Italian Bioethics Board (Comitato nazionale di bioetica, Cnb) of the Italian Ministry of Health [39] on robotics and roboethics, the exit strategy of engAGE aims to do the following:

Promote adequate experimentation of robotics in field assistance to ensure conditions for physical and psychological integrity of the end user, explaining the risks and benefits, highlighted also in the informed consent form.Ensure both equitable access to robotic and general technologies and the use of robots to assist and not to replace humans in order to avoid delegating the irreplaceable human task of care and assistance to the machine.Demonstrate that the introduction of robotics in medicine entails always the real consideration of benefits; of the complexity of the change, complete with the structure of the services; and of the economic burden that this entails.

Users who took part in the study did not incur any direct or indirect costs related to the use of the technology platform. The platform was provided to them by the pilot sites and had to be returned to the research team at the end of the trial.

